### Data management and monitoring

Data on the participants will be collected during the eligibility assessment. Signed consent forms will be safeguarded. This study will be performed in accordance with the approved protocol. If a participant is excluded or withdraws from the study, the reason for the exclusion will be recorded.

Due to the simplicity and safety of the protocol, we do not expect the participants to experience any adverse events. If the participant presents any side effect related to the intervention process, such as itching, burning sensation, headache, or pain, the event will be reported to the ethics committee and procedures will be performed to ensure the participant's safety. Adverse events will be carefully monitored during this study. The team at the clinical intervention sites will monitor and report all minor and serious adverse events that occur, if any, from enrollment to the end of the study. The researchers will also make telephone calls one day after each session of the intervention for clinical follow-up of the participant.

Descriptive data will be recorded using electronic anthropometric forms and registration forms that will be filled out and sent to the data analyst of the Human Movement Analysis laboratory at Universidade Evangélica, Goiás, Brazil. The data will be entered into a study-specific database by trained staff. The study will be carried out by a multidisciplinary team linked to the Movement Analysis Laboratory of the University Evangelica, Goias, Brazil, composed of clinical researchers, the School of Medical Sciences of São Paulo, São Paulo, Brazil, the Politecnico di Milano, Milano, Italy, and the Strathclyde University, Glasgow, Scotland.

The researchers will have weekly calls to track the progress of the study and ensure adherence to the design, schedule, and budget.

An endpoint adjudication committee led by [name] will meet to review, have access to these interim results and make the final decision to terminate the study.

The Data Security and Monitoring Board is independent and consists of a statistician, clinical researchers, health science specialists, data engineering specialist, and specialists in the use of tDCS and VR.

Retention activities are proactive. The participants will receive text messages or phone calls reminding them of their upcoming field trips. During all visits, the participants will be welcomed by the technical team and offered personalized attention, study-focused counseling, linking to appropriate services, high quality standard of clinical care through regular staff training and telephone calls on days following the sessions to identify any adverse effects.

### Recruitment

Strategies will be employed to encourage participation in the study and reduce the dropout rate. The children with DS will be recruited from the outpatient clinic of the University Center of Anápolis and the Association of Parents and Friends of Exceptional Children of Anápolis. Parents/guardians will be contacted by telephone (or other means of communication). Pamphlets will be created with a brief description of the objectives, type of therapeutic intervention, expected results and eligible population. The researchers of the project will be responsible for this disclosure as well as leaving contact information for the parents of eligible children. The children selected for this study will be recruited according to the schedule registered with the ethics committee and REBEC in December 2020.

#### Study 1

A cross-sectional study will be conducted to determine the pattern of normality in children with typical development and compare the pattern to that found in children with DS. The sample selected for this study will be in accordance with the eligibility and quantity criteria for a convenience sample. The participants will be divided into two groups and each group will consist of 12 children.

#### Study 2

A pilot study will be conducted to determine the sample size for the randomized controlled clinical trial. For the proper sample size calculation, the pilot study will be carried out using the same methods as those to be employed in the main study and will involve ten children selected based on the eligibility criteria for the children with DS. The sample size for the clinical trial will be calculated based on the means obtained in the experimental and control groups of this pilot study, considering brain activity as the primary outcome, a unidirectional alpha of 0.05 and a power of 80%. The sample size will be then increased by 20% to compensate for possible dropouts.

#### Study 3

A randomized controlled trial will be conducted. The sample will be selected based on the results of the pilot study and the children will be randomly distributed into two groups using a randomization website (www.random.org).

The experimental group is as follows: anodal tDCS (anode placed over F3 of the International 10-20 Electroencephalogram System and cathode placed over right deltoid muscle) combined with VR training.

The control group is as follows: sham tDCS (same electrode montage as in the experimental group) combined with VR training. At the end of the study, children in the sham group will receive the same stimulation protocol as the experimental group as a form of treatment to enable the same gain in functioning that we expect to find in the experimental group.

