## Objective/hypotheses

The objective of the study is to perform a comparative analysis of brain activity, muscle activity and upper limb kinematics during the execution of a manual motor task motivated by a VR game during anodal tDCS in children with DS. Psychomotor, muscle, and cognitive skills will be assessed before and after the intervention as well as at the 1-month follow-up. The objectives of the study will be to (I) correlate variables related to movement kinematics, motor activity, and brain activity, (II) compare the effects of transcranial stimulation in children with DS and those with typical development (TD), (III) determine the effects and possible adverse effects of anodal tDCS at an intensity of 1 mA administered during 20 min of training in children with DS, and (IV) determine the effects of different anodal tDCS montages in children with DS.

The null hypothesis of the study is that the results of ten sessions of anodal tDCS over the F3 region of the cortex during a motor task motivated by a VR game will not differ significantly from the results obtained from ten sessions of sham tDCS with the same training in children with DS. The alternative hypothesis is that the results of ten sessions of anodal tDCS over the F3 region of the cortex during a motor task motivated by a VR game will differ significantly from the results obtained from ten sessions of sham tDCS with the same training in children with DS.

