### Sample size

A convenience sample will be used in phase 1, which will be an exploratory analysis to identify and compare the profile and motor variables of children with DS and TD. Phase 2 will be a pilot study with a random, exploratory sample using the formula of Student’s *t*-test with a minimum power of 80% (power equal to type II error) and 5% significance level (power equal to type I error) to furnish the calculation of the sample size for phase 3. Phase 3 will be a randomized controlled clinical trial with the sample size based on the findings of phase 2.

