## Statistical analysis of results

Statistical analysis will involve the calculation of mean, standard deviation, minimum and maximum values for the descriptive analysis of the effects of tDCS and VR on the quantitative variables. The Shapiro-Wilk normality test will be used to determine the distribution of the data in terms of adherence to the Gaussian curve. Parametric variables will be expressed as mean and standard deviation. Nonparametric variables will be expressed as median and interquartile range.

For phase 1, either Student’s *t*-test or Mann-Whitney test will be used to compare quantitative variables between the TD and DS groups. In phase 2, descriptive measures of mean and standard deviation will be used as initial values for the calculation of the sample size in phase 3. In phase 3, we will analyze quantitative variables with measures over time (pre-intervention, post-intervention and one-month follow-up) and comparisons of the EG and CG will be performed using repeated-measures ANOVA. The level of significance will be set at 5% for all statistical tests. The data will be organized, tabulated and analyzed with the aid of the Statistical Package for the Social Sciences (v.25.0).

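### Phase 3 is sized with a one-sided 5% alpha on the observed means of a ten-child pilot, while the hypotheses and the planned test are non-directional at 5%

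*Protocol article*

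**What the plan says.** All references are to the protocol article.

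- **Recruitment, Study 2.** The pilot involves ten children with Down syndrome. Its two arm means supply the target difference for phase 3, and the calculation is made "considering brain activity as the primary outcome, a unidirectional alpha of 0.05 and a power of 80" percent. The result is then raised by 20% for dropout.
- **Sample size.** The formula is that of Student's t-test, "with a minimum power of 80% (power equal to type II error) and 5% significance level". Sidedness is not given here.
- **Statistical analysis of results.** From the pilot, "descriptive measures of mean and standard deviation will be used as initial values for the calculation of the sample size in phase 3". Phase 3 compares the two groups over three time points by repeated-measures ANOVA. "The level of significance will be set at 5% for all statistical tests".
- **Objective/hypotheses.** The null is no difference. The alternative is that results under active stimulation "will differ significantly from the results obtained from ten sessions of sham tDCS".
- **Study design.** Allocation is 1:1, and superiority of the experimental group is expected.

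The article gives no phase 3 sample size, target difference or SD.

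**The concern.** The sizing rule spends the whole 5% in one direction. The hypotheses allow a difference in either direction, and an ANOVA F test at 5% detects either. No section specifies a one-sided test. A size that gives 80% power for the easier one-sided test does not give it for the same comparison made two-sided.

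The second weakness is the source of the target difference. It is whatever difference the pilot happens to show, not one judged worth detecting. A pilot of ten children estimates that difference so loosely that the resulting n is largely a matter of chance.

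Phase 3 rests entirely on this rule. If it stands, the trial may report a design power its own test does not have, and a null result may be read as stronger evidence of no effect than it is.

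**Working it through.** **Inputs.** From the article: one-sided alpha 0.05, power 80%, t-test formula, 1:1 allocation, 20% added for dropout, ten pilot children, non-directional ANOVA at 5%. Assumed, because the article gives none: standardised differences d of 0.5 to 1.2, and a pilot split of 5 v 5. With no N, difference or SD stated, there is no stated sample size to reproduce. The only stated figure is the 80%, which the one-sided rule meets by construction.

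**1. Sidedness, for the t-test (normal approximation; independent of d).**
- One-sided sizing sets the standardised signal at 1.645 + 0.842 = 2.486 (from unrounded values).
- Tested two-sided at 5%: power = Φ(2.486 − 1.960) = Φ(0.526) = 0.70.
- n ratio needed to match: ((1.960 + 0.842) / 2.486)² = 1.27.

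Exact noncentral-t results, per arm before dropout:

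| Assumed d | n, one-sided | Two-sided power at that n | n, two-sided |
|---|---|---|---|
| 0.5 | 51 | 70.6% | 64 |
| 0.8 | 21 | 71.6% | 26 |
| 1.0 | 14 | 72.1% | 17 |
| 1.2 | 10 | 71.8% | 12 |

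**2. The 20% allowance.**
- Nobody drops out (1.2n): Φ(2.486 × √1.2 − 1.960) = Φ(0.764) = 0.78.
- 20% drop out (1.2 × 0.8 = 0.96n): Φ(2.486 × √0.96 − 1.960) = Φ(0.476) = 0.68.

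**3. The repeated-measures test at the same n.** Assume 51 per arm, d = 0.5, compound symmetry with within-child correlation ρ, no baseline difference, and the same effect at both later visits.
- Group-by-time term: noncentrality (51/2) × (2/3) × 0.25 / (1 − ρ) = 4.25 / (1 − ρ), on 2 and 200 df.
- Group main effect: noncentrality (51/2) × (4/9) × 0.25 × 3 / (1 + 2ρ) = 8.5 / (1 + 2ρ), on 1 and 100 df.

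| ρ | Group-by-time power | Group main-effect power |
|---|---|---|
| 0.3 | 58% | 63% |
| 0.5 | 74% | 53% |
| 0.6 | 83% | 50% |
| 0.7 | 93% | 46% |

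**4. The pilot difference as target (5 v 5 assumed).**
- 95% half-width in SD units: t(0.975, 8 df) × √(2/5) = 1.46.
- Probability that the pilot points the wrong way, Φ(−d√(5/2)): at d = 0.5, Φ(−0.791) = 21%; at d = 0.8, Φ(−1.265) = 10%.
- Simulation (200,000 pilots per d, normal approximation for n and power), restricted to pilots with a positive effect. Power is for the two-sided t-test at the true d.

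| True d | Sizing | Interquartile range of n per arm | Median true power | Below 80% |
|---|---|---|---|---|
| 0.5 | one-sided | 10 to 92 | 44% | 69% |
| 0.5 | two-sided | 13 to 117 | 52% | 65% |
| 0.8 | one-sided | 7 to 45 | 59% | 63% |
| 0.8 | two-sided | 9 to 57 | 69% | 57% |

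Aligning the sidedness therefore does not by itself make the nominal 80% dependable.

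**The case against.** The best defence is that Study design expects superiority of the experimental group, so one-sided sizing was deliberate. That may explain the choice. It does not carry through: the formal hypotheses have no direction, and neither does the planned F test.

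A reader might infer that the trial's true power is simply 70%, or that 80% cannot be reached. The article does not support that. The 70% belongs to a two-sample t-test with the assumed effect exactly true. The planned analysis is a repeated-measures ANOVA, and step 3 shows its power on either side of 80%, depending on a correlation and a choice of term that the article does not use for sizing. The same point means the repeated measures cannot be relied on to supply the stated 80%. The dropout allowance also softens the loss when few children leave, though in general to about 78%.

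It is fair to add that the 5 v 5 split is inferred, and that with no N stated this is an inconsistency in the specification, not a wrong computed result. The wording under Sample size that equates 80% power with the type II error changes no number and is editorial.

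**Conclusion.** The sizing rule is wrong as written: one-sided in Recruitment, non-directional in Objective/hypotheses and Statistical analysis of results. For the t-test named under Sample size, with the assumed effect true, the stated 80% becomes about 70% two-sided (78% with the allowance fully retained, 68% with 20% dropout), and a matching calculation needs about 1.27 times the n. These figures do not depend on the unstated difference or SD. For the repeated-measures test, neither 70% nor 80% is established.

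The reliance on pilot means is a separate defect and remains once sidedness is aligned. Assuming 5 v 5, the target has a 95% half-width of about 1.46 SD, and the pilot points the wrong way in about 21% of cases at a true d of 0.5 and 10% at 0.8.

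The article has not yet set the phase 3 number, so both can be corrected before it is.

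**What to change.** 1. In Recruitment, Study 2, replace the one-sided alpha with a two-sided alpha of 0.05, in line with the hypotheses and the planned analysis.
2. Base the target on a smallest worthwhile difference in the primary EEG variable, fixed before the pilot is read. Use the pilot for the SD only. Any allowance for the imprecision of that SD is for the trial statistician to choose.
3. If the number of children cannot grow, state the two-sided power over a prespecified range of true differences. Do not quote 80%, and do not replace it with a single 70%, which holds only if the pilot effect is exactly true.
4. Under Sample size, correct the wording: 80% power corresponds to a type II error of 20%.

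The cost is either a larger calculated n (about 1.27 times from sidedness alone, more if an SD allowance is added) or a less favourable stated power. The smallest worthwhile EEG difference also has to be agreed and justified, which takes more work than the change of wording.

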### Evaluation process

Evaluations in the cross-sectional study, pilot study, and clinical trial (pre-intervention, post-intervention and one-month follow-up) will be performed in accordance with Resolution No. 466/12 of the Brazilian National Board of Health. Each evaluation session will last a maximum of 1 h and 30 min.

Evaluations will be performed at the Movement Analysis Laboratory of the University Center of Anapolis. Brain activity will be measured through the acquisition of electroencephalographic (EEG) signals. Muscle activity will be determined through the acquisition of electromyographic (EMG) signals. Three-dimensional motion analysis will be used for the acquisition of the kinematic data.

Initially, the identification form will be completed and the anthropometric data will be collected. The participants will be assessed using a non-immersive virtual reality motor task on a Dell S2240T LED 21.5″ touch screen monitor. The game will consist of figures displayed in random order. The child will be instructed to touch only the figures indicated in the corner of the screen, performing a reaching motor task combined with a cognitive task of memorization and attention. After each tap (trial), the individual will return the hand to the initial support position and wait for a correct new figure to be displayed.

During the task, the EEG signals, EMG signals, and upper limb kinematic data will be collected for the determination of neural signals associated with movement.

#### Electroencephalographic analysis

Brain activity will be investigated by electroencephalography using the eego™ sports equipment concomitantly to electromyography and the kinematic analysis. The EEG equipment is a battery-powered system with 64-channel EEG recordings and sampling up to 16 kHz.

EEG is a method for assessing the relationship between the brain and behavior and provides a direct real-time measure of neural activity, identifying critical neural mechanisms for motor performance and facilitating the recognition and modification of mental states associated with certain cortical arousal patterns and concomitant behavioral outcomes [30–33].

The task will be performed in a small room without the possibility of external noise. Only the evaluator and child will be present. The child will be placed in the upright position on a chair adjusted so that the feet rest comfortably on the floor. The child will be seated at a square table on which the hands will rest in the starting position. A memory game will be projected on a touch monitor with possibilities of advancement in difficulty level and the subjective measurement of hits and misses. The participant will be oriented to perform a manual motor task—touching the screen to match figures during the memory game. After each touch (trial), the hand will return to the initial position. The task will be performed concomitantly with the EEG reading to identify neural signals associated with the movement.

The data will be preprocessed using the *asa™* software, which is a highly flexible EEG/ERP and magnetoencephalography (MEG) analysis package with a variety of source reconstruction and signal analysis features [34].

#### EMG analysis

Activity of the brachial biceps and triceps muscles during the manual motor task will be determined using EMG. Electrical activity resulting from activation of the elbow flexors and extensors will be collected using an eight-channel electromyograph (FREEEMG, BTS Engineering) with a bioelectric signal amplifier, wireless data transmission, and bipolar electrodes with a 2000-fold total gain and frequency ranging from 20 to 450 Hz. The impedance and common rejection mode ratio of the equipment is > 1015 Ω/0.2 pF and 60/10 Hz 92 dB, respectively. The motor point of the muscles will be identified for electrode placement and the skin will be cleaned with 70% alcohol to reduce bioimpedance, following the guidelines of the Surface Electromyography for Noninvasive Muscle Assessment [35]. All EMG data will be scanned at 1000 frames per second using the BTS MYOLAB software program.

#### Three-dimensional motion analysis

Upper limb motion kinematics will be evaluated using the SMART-D 140 system (BTS, Milan, Italy) (Fig. 2), with eight infrared-sensitive cameras, a sampling frequency of 100 Hz and video system synchronized with the SMART-D system. Passive markers will be positioned at anatomical landmarks directly on the skin with specific tape following the SMARTup protocol: the experimental setup (Fig. 2) [35–38]. A total of 18 markers measuring 15 mm in diameter will be used to identify the position of the head, trunk and upper limbs (arm, forearm, and hand).

**Fig. 2 Fig2:**
[figure not shown]
Placement of markers for three-dimensional analysis using SMARTup: the experimental setup. Menegoni et al. Europeun Journal Neurologic 2009 [36]

**Fig. 3 Fig3:**
[figure not shown]
Equipment and execution of reaching/cognitive task

The data from all equipment (SMART-D 140, BTS, Milan, Italy [35–39]; FREEEMG, BTS Engineering [34]; and eego™ mylab) will be collected simultaneously during the reaching task with a cognitive component. The participant will be positioned on a chair with his/her arms on the evaluation table in front of a touch monitor, which will display figures in random order. The child will be instructed to touch only the figures indicated in the corner of the screen, performing a reaching task combined with a cognitive task of memorization and attention. After each tap (trial), the hand should return to the initial support position until a new correct figure is displayed (Fig. 3).

**Fig. 4 Fig4:**
[figure not shown]
Anode (pink) and cathode (blue) placement and virtual reality training and this should be in the section: Transcranial direct current stimulation (tDCS)

### Intervention protocol

The therapeutic intervention will only be performed in studies 2 and 3 of this protocol and will consist of a combination of tDCS and VR. The protocol will follow the safety procedures described in the literature for the use of tDCS in the population with neurological disorders [40–48]. Three 20-min sessions of tDCS concomitant with VR will be held for a total of ten sessions [42–48]. Training will be preceded by fitting and adapting the equipment to the participant. During the clinical trial, participants will be prohibited initiate therapeutic activities that may be similar in terms of the biomechanics used for the tests and intervention.

Since the protocol is an intervention with rehabilitation for motor and intellectual training, the participants will be asked to report participation in any other activities for the biomechanical investigation of the activity, as this population may need rehabilitation outside the study to maintain their daily routines. It will be up to the researchers to identify whether such activities may compromise the study results.

#### Transcranial direct current stimulation (tDCS)

Stimulation will be administered using a tDCS device (DC-Stimulator NeuroConn, Germany) and two sponge (non-metallic) surface electrodes measuring 25 cm^2^ (5 × 5 cm) soaked in saline. The participants will be randomly allocated to two types of treatment: (1) active anodal tDCS and (2) sham tDCS. The anode will be positioned over F3 of the international 10-20 electroencephalogram system and the cathode will be positioned over the right deltoid muscle. This montage (Fig. 4) will enable the administration of anodal tDCS over the dorsolateral prefrontal cortex (DLPFC) while minimizing the effect of cathodal stimulation of the brain. The 1 mA current (current density: 0.029 mA/cm^2^) will be administered over the DLPFC for 20 min during upper limb training. The stimulator has a button that allows the operator to control the intensity of the current. Stimulation will be gradually increased to 1 mA at the beginning of the session and gradually decreased during the final 10 s of the session. Sham stimulation will consist of the same electrode montage and the stimulator will be turned on for 30 s, giving the child the initial sense of stimulation, but no current will be delivered for the remainder of the session. This is considered a valid control procedure in studies involving tDCS [40–48]. The participants will undergo a rehabilitation program while receiving tDCS. The rehabilitation program is based on the serial reaction-time task, which has been used extensively in upper limb studies. During the experiment, the participants will be seated on a chair in front of a touch screen monitor, head, and arms supported (ankle angle: ~ 110°; knee angle: ~ 150°; hip angle: ~ 120°). The participants will be instructed to avoid drinking coffee or consuming other stimulants on the day of the trial.

